## Abstract

**Background::**

Upper gastrointestinal disorders are common in clinical practice, for example, gastritis, peptic ulcer disease, and gastroesophageal reflux disease. Panendoscopy or upper gastrointestinal endoscopy is viewed as the primary tool for examining the upper gastrointestinal mucosa, and permitting biopsy and endoscopic therapy. Although panendoscopy is considered to be a safe procedure with minimal complications, there are still some adverse effects, and patients are often anxious about undergoing invasive procedures. Traditional Chinese medicine tongue diagnosis plays an important role in differentiation of symptoms because the tongue reflects the physiological and pathological condition of the body. The automatic tongue diagnosis system (ATDS), which noninvasively captures tongue images, can provide objective and reliable diagnostic information.

**Methods::**

This protocol is a cross-sectional, case-controlled observational study investigating the usefulness of the ATDS in clinical practice by examining its efficacy as a diagnostic tool for upper gastrointestinal disorders. Volunteers over 20 years old with and without upper gastrointestinal symptoms will be enrolled. Tongue images will be captured and the patients divided into 4 groups according to their panendoscopy reports, including a gastritis group, peptic ulcer disease group, gastroesophageal reflux disease group, and healthy group. Nine primary tongue features will be extracted and analyzed, including tongue shape, tongue color, tooth mark, tongue fissure, fur color, fur thickness, saliva, ecchymosis, and red dots.

**Objectives::**

The aim of this protocol is to apply a noninvasive ATDS to evaluate tongue manifestations of patients with upper gastrointestinal disorders and examine its efficacy as a diagnostic tool.

## Introduction

1

Upper gastrointestinal disorders associated with a range of troublesome symptoms are common in clinical practice, such as gastritis, peptic ulcer disease (PUD), and gastroesophageal reflux disease (GERD), among others. The most common symptoms of upper gastrointestinal disorders are abdominal pain or epigastric pain, and heartburn.^[1]^ It can be estimated that more than half of the world's population suffers from gastritis to some degree.^[2]^ It has also been reported that the annual incidence of PUD ranges from 0.10% to 0.19% for physician-diagnosed PUD,^[3]^ and that the prevalence of GERD is estimated to be 18.1% to 27.8% in North America, 8.8% to 25.9% in Europe, and 2.5% to 7.8% in East Asia.^[4]^ However, these may be underestimates due to the absence of symptoms in some cases and undiagnosed occurrences. If individuals ignore the warning signs or their symptoms are not properly diagnosed and managed, there can be severe complications. For example, patients with PUD are at risk for gastroduodenal hemorrhage or perforation, GERD is associated with Barrett esophagus, and chronic gastritis may be related to gastric cancer.

Panendoscopy, also referred to as upper gastrointestinal endoscopy and esophagogastroduodenoscopy (EGD), is the primary tool used for examining the upper gastrointestinal mucosa, and permits biopsy and endoscopic therapy.^[1]^ Panendoscopy is considered to be a safe procedure with minimal complications. However, there are still several risks associated with this procedure. The most frequent complications are associated with therapeutic interventions and include perforation, cardiac, or respiratory complications related to underlying comorbidities, and adverse effects from anesthesia.^[5]^ In addition, anxiety about undergoing invasive procedures is a serious problem in some patients. High levels of anxiety may lead to incomplete procedures, a higher chance of complications, or patients refusing endoscopy.^[6]^

Diagnosis in traditional Chinese medicine (TCM) is based on 4 procedures, observation, smelling or listening, inquiry, and palpation. Tongue diagnosis plays an important role in inspection and helps to differentiate between symptoms. The tongue is considered to reflect the physiological and pathological condition of the body, as well as the degree and progression of disease, through the meridians that connect the tongue to the internal organs.^[7,8]^ However, the result of tongue diagnosis often depends on subjective judgments and environmental factors.^[9]^ To obtain objective and quantitative diagnosis, many computerized tongue diagnosis systems have recently been developed.^[10]^ Several studies have used computerized tongue analysis to evaluate the relationship between tongue manifestations and various diseases, including rheumatoid arthritis,^[11]^ breast cancer,^[12,13]^ type 2 diabetes,^[14]^ metabolic syndrome,^[15]^ eczema,^[16]^ and dysmenorrhea,^[17]^ but seldom has the research focused on upper gastrointestinal disorders. The automatic tongue diagnosis system (ATDS) has shown high consistency and can provide objective and reliable information and analysis of tongue features, facilitating doctors in making effective observations and diagnoses of specific diseases.^[18]^

The objectives of this protocol are to apply the noninvasive ATDS to evaluate tongue manifestations in patients with upper gastrointestinal disorders, and to provide valuable information for clinical doctors, which can be used to facilitate the early detection and diagnosis of upper gastrointestinal disorders, to analyze the current status of patients, and to dynamically schedule treatment plans.

## Methods

2

### Ethics approval

2.1

This protocol has been reviewed and approved by the Institutional Review Board of the Chang Gung Medical Foundation (IRB no. 104-4725B). The protocol identification number at https://clinicaltrials.gov is NCT03258216. This study is conducted in accordance with the principles of the Declaration of Helsinki. Written informed consent will be obtained from all patients before enrollment. Personal information about potential and enrolled participants will be collected, shared, and maintained in an independent closet in order to protect confidentiality before, during, and after the trial.

### Participants

2.2

Patients will be recruited from the outpatients of the Department of Hepatogastroenterology of Kaohsiung Chang Gung Memorial Hospital (KCGMH) in Kaohsiung, Taiwan.

Patients will be eligible if they satisfy the following criteria: age over 20 years old; with upper gastrointestinal symptoms, or who without symptoms and visit clinic for health examination; meet the criteria for examination via endoscopy; volunteered to join this research and signed the institutional review board agreement. Both men and women will be enrolled.

Patients with any of the following conditions will be excluded: hypertension, diabetes, hepatitis, or other systemic diseases; pregnancy; acute infection; cognitive impairment; unable to protrude the tongue stably; risk of temporomandibular joint dislocation.

### Study design

2.3

This protocol is a cross-sectional, case-controlled observational study investigating the usefulness of the ATDS in clinical practice by examining its efficacy as a diagnostic tool for upper gastrointestinal disorders.

After giving their consent, participants will undergo tongue image capturing using the ATDS. The ATDS examination will be performed under constant environmental conditions and by the same educated operator. After capturing tongue image, participants accept panendoscopy which will be performed by a professional gastroenterology doctor. According to findings of panendoscopy, the participants will be allocated to the following 4 groups: a peptic ulcer disease group (PUD, including patients diagnosed with peptic ulcers), a gastroesophageal reflux group (GERD, including patients diagnosed with reflux esophagitis or gastroesophageal reflux), a gastritis group (GA, including patients diagnosed with gastritis), and a healthy group (H, including patients with negative results from the gastric endoscopy procedure). A flow chart of the trial design is presented in Fig. 1.

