### Data analysis

2.7

All statistical analyses will be performed using the SPSS statistical package program, version 17.0 (SPSS Inc., Chicago, IL). Chi-square tests will be applied for categorical data and Analysis of variance tests will be applied for continuous data. Logistic regression will be used to estimate the odds ratio and the probability of a binary response, based on one or more independent variables. *P*-values <.05 will be considered statistically significance.

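### The four endoscopy groups do not form a partition: a patient with two diagnoses meets two definitions, a patient with only another finding meets none, and no allocation rule is stated

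*Protocol article*

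**What the plan says.** The abstract of the protocol article describes "the patients divided into 4 groups according to their panendoscopy reports", and section 2.3 (Study design) repeats this: "According to findings of panendoscopy, the participants will be allocated to the following 4 groups". The definitions in section 2.3 are:

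- PUD: "a peptic ulcer disease group (PUD, including patients diagnosed with peptic ulcers"
- GERD: "including patients diagnosed with reflux esophagitis or gastroesophageal reflux"
- GA: "a gastritis group (GA, including patients diagnosed with gastritis"
- H: "a healthy group (H, including patients with negative results from the gastric endoscopy procedure"

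On the comparison, section 2.7 (Data analysis) says "Chi-square tests will be applied for categorical data and Analysis of variance tests will be applied for continuous data", and adds logistic regression for a binary response. The Discussion (section 3) says that the differences between the three diseases are of interest. The Introduction (section 1) remarks that "more than half of the world's population suffers from gastritis to some degree".

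**The concern.** Each disease definition asks whether one diagnosis is present. None asks whether the others are absent. The definitions therefore do not produce the four-way division that the abstract announces.

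Chi-square and one-way ANOVA across the groups assume that every patient contributes once, to one group. With no stated rule, two analysts holding identical endoscopy reports could form different groups and reach different results. Even a sensible hierarchy, such as placing every patient with reflux in GERD, would leave gastritis mixed into the PUD and GERD groups. Their contrasts with GA would then no longer compare one disease with another, which is what the Discussion sets out to do.

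**Working it through.** **1. Definitions against possible reports.** Apply the four definitions of section 2.3 as written:

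| Findings in the report | Groups whose definition is met | Number |
|---|---|---|
| Ulcer only | PUD | 1 |
| Reflux only | GERD | 1 |
| Gastritis only | GA | 1 |
| No finding | H | 1 |
| Ulcer and gastritis | PUD, GA | 2 |
| Reflux and gastritis | GERD, GA | 2 |
| Ulcer and reflux | PUD, GERD | 2 |
| All three | PUD, GERD, GA | 3 |
| Another finding only | none | 0 |

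Four of the nine patterns lead to exactly one group. H is the only group that is disjoint from the others by definition.

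**2. Search for a rule elsewhere.** The exclusions in section 2.2 do not cover patients with several upper gastrointestinal findings. Section 2.5.2 says only that the endoscopy reports are recorded. Section 2.7 gives no hierarchy, principal-diagnosis rule or mixed group. Figure 1 (the flow chart) is not visible in the text at hand.

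**3. Possible scale.** The documents give no overlap figure to reproduce. The planned total of 517 (section 2.6) comes with no expected group sizes. Assume gastritis in 50% of patients (the Introduction says more than half of the world's population), independent of the other diagnoses. Then about half of PUD and GERD patients also meet the GA definition. As a share of the sample:

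- Low end, GERD at the East Asian population prevalence quoted in the Introduction (2.5% to 7.8%), PUD ignored: 0.5 × 2.5% = 1.3% and 0.5 × 7.8% = 3.9%, or about 6 to 20 of 517.
- High end, PUD and GERD each a quarter of the sample: 0.5 × (25% + 25%) = 25%, or about 129 of 517.

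Recruitment is from a hepatogastroenterology clinic, so population prevalence is a weak guide to case mix. The documents do not say where in this range the study will fall.

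**4. Cost if patients with two diagnoses were dropped.** Completers after 10% drop-out: 517 × 0.9 = 465. Assume equal groups, so three quarters are diseased, and let q be the share of diseased patients with two diagnoses. Then N = 465 × (1 − 0.75q). Take f = 0.175, the effect size at which a four-group ANOVA has about 90% power with 465:

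| q | N | Power |
|---|---|---|
| 0 | 465 | 0.90 |
| 0.20 | 395 | 0.84 |
| 0.40 | 326 | 0.75 |

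**5. Direction of bias if they were kept in GERD.** Let GERD shift a tongue feature by g and gastritis by a, additively, in standard deviation units. Suppose half the GERD group also has gastritis. The contrast between the pure diseases is g − a. The contrast actually estimated is (g + 0.5a) − a = g − 0.5a.

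| g | a | Pure contrast | Estimated contrast |
|---|---|---|---|
| 0.3 | 0 | 0.30 | 0.30 |
| 0.6 | 0.3 | 0.30 | 0.45 |
| 0.3 | 0.6 | −0.30 | 0.00 |

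The contrast can be unchanged, inflated or removed. The same algebra applies to PUD against GA.

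**The case against.** The strongest reply is that this is a condensed article. The words for dividing and allocating show that one group per patient is intended, and the handling of double findings could stand in a fuller document or in Figure 1. That intention is fair to grant. The reply does not remove the point: group membership is the study's central classification, the article chose to set it out, and the rule as set out fails for any patient with two findings.

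It is also right that the logistic regression in section 2.7 does not need four disjoint groups, since each diagnosis can be modelled as present or absent. The requirement attaches to the chi-square and ANOVA comparisons. It could further be said that a negative endoscopy means negative for the three named diseases only. A patient with another lesion would then be counted as healthy, which is no better.

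Four stronger readings are tempting but not supported:

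- *Patients will be counted twice.* No section plans this. Had it been planned, a simulation with 465 distinct patients gave an ANOVA type I error of 0.049 with no overlap, 0.035 with 20% of diseased patients duplicated and 0.027 with 40%. The nominal level is lost, but in the conservative direction.
- *Most PUD and GERD patients will have gastritis.* The Introduction's figure concerns the world's population and gastritis of any degree. It is not a rate of endoscopic diagnosis in this clinic.
- *The disease contrasts will shrink towards zero by a known amount.* Step 5 of the working shows that this depends on the unknown separate effects.
- *Labels will be chosen with tongue results in view.* Groups follow from panendoscopy reports written by gastroenterologists, and nothing says otherwise. No rule prevents it either, but that is a gap and not evidence of a practice.

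**Conclusion.** The point holds as a defect in the allocation rule. The stated definitions are neither mutually exclusive nor exhaustive, while two of the planned analyses and a stated aim depend on a clean division. That conclusion follows from the text of section 2.3 and needs no assumption beyond there being no rule in the unseen figure.

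The size cannot be fixed from the documents. The range for overlap rests on 50% gastritis, independence and assumed shares of PUD and GERD. The power losses rest on equal groups, assumed overlap rates and the dropping of every patient with two diagnoses. Both are illustrations and not forecasts. What can be said is that overlap may be substantial among PUD and GERD patients, that its share of the whole sample is unknown, and that the direction of any bias is not predictable.

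**What to change.** 1. From the same endoscopy report, code PUD, GERD and gastritis as three separate yes/no indicators. Relate each tongue feature to the three jointly in one model, so that each association is adjusted for the other two diagnoses.
2. For the four-group table, write down an allocation rule for multiple findings and fix it before any tongue data are examined.
3. Repeat the four-group comparison in patients with a single diagnosis, with H retained, as a sensitivity analysis.
4. Define H as none of the three diagnoses and no other lesion. Leave patients with only other findings out of the four groups and report their number.

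The cost is protocol wording and one extra coding step, with no new data. Intervals will be wider where diagnoses coincide often, because the data then carry less information for separating them.

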**Figure 1 F1:**
[figure not shown]
Flow chart of the study design. ATDS = automatic tongue diagnosis system; GERD = gastroesophageal reflux disease; PUD = peptic ulcer disease; UGID = upper gastrointestinal disease.

### Intervention: automatic tongue diagnosis system

2.4

As shown in Fig. 2, the ATDS was developed to capture tongue images and reliably analyze tongue features. The system has 3 major functions: image capturing and color calibration, tongue area segmentation, and tongue feature extraction.

**Figure 2 F2:**
[figure not shown]
Components of the automatic tongue diagnosis system.

To reduce the influence of background surroundings, the ATDS is placed in a set location and the operator and the patient sit on fixed seats. To start, the well-trained operator adjusts the chin support horizontally and vertically in order to capture the whole tongue. Then, the patient protrudes their tongue and holds it relaxed and stable for about 5 seconds, allowing the operator to capture a tongue image.

The ATDS can automatically correct any lighting and color deviation caused by changes in background lighting using a color bar attached beside the chin support. After capturing, the tongue images are prepared by isolating the tongue region to eliminate any irrelevant sections of the image including the teeth, lower facial portions, or background surrounding the tongue. After this, feature identification and extraction can be carried out.

### Outcome measures

2.5

#### Primary outcome measures

2.5.1

Nine primary tongue features will be extracted from the ATDS as follows: tongue shape: small and thin, moderate, large, and fat; tongue color: slightly white, slightly red, red, dark red, and dark purple; tooth mark: includes number, average covering area, maximum covering area, minimum covering area, and organs corresponding to the covering area; tongue fissure: amount, average covering area, shortest length, and longest length; fur color: white, yellow, and dye; fur thickness: none, thin, thick; fur amount, average covering area, maximum covering area, minimum covering area, and organs corresponding to the covering area; saliva: includes total area and the amount of saliva (none, little, normal, excessive); ecchymosis: amount, average covering area, maximum covering area, minimum covering area, and organs corresponding to the covering area; red dots: number, average covering area, maximum covering area, minimum covering area, and organs corresponding to the covering area.

Feature identification will be further subdivided into 5 segments (spleen–stomach, liver-gall-left, liver-gall-right, kidney, and heart–lung area) according to the theory of traditional Chinese medicine.

#### Secondary outcome measures

2.5.2

Panendoscopy reports written by professional gastroenterology doctors will be recorded.

### Sample size

2.6

We calculated the sample size will be 517 with power = 0.9, alpha = 0.05, effect size convention *r* = 0.3, and an anticipated drop-out rate of 10%, using G∗Power 3.0.1.0 software which is download from http://www.gpower.hhu.de.

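### The stated inputs (r = 0.3, power 0.9, alpha 0.05, 10% drop-out) do not give 517 under a correlation or under the planned chi-square or ANOVA tests, so the 90% power does not describe the four-group study

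*Protocol article*

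**What the plan says.** Section 2.6 (Sample size) gives one total with its inputs: "We calculated the sample size will be 517 with power = 0.9, alpha = 0.05, effect size convention" r = 0.3, and a 10% drop-out allowance, computed in G*Power. It names no test, sidedness, number of groups or outcome.

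Section 2.3 (Study design) says that "According to findings of panendoscopy, the participants will be allocated to the following 4 groups": peptic ulcer disease, gastro-oesophageal reflux disease (GERD), gastritis and healthy. Group sizes follow from the endoscopy findings, and no ratio is fixed.

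Section 2.7 (Data analysis) says "Chi-square tests will be applied for categorical data and Analysis of variance tests will be applied for continuous data". It adds logistic regression for a binary response, without an odds ratio or event rate. Neither a correlation analysis nor a two-sample t-test is listed.

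**The concern.** A sample size statement should let a reader recover the number from its inputs and see which comparison the power refers to. Here the effect is on the correlation scale, the planned tests compare four groups, and the total is about twice or more what a 0.3 effect requires on the r, w or f scale.

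The interpretation of the results depends on this. If 517 was built on a smaller effect than r = 0.3, a reader will take the wrong detectable effect from section 2.6. A null comparison between two of the endoscopy groups could then be read as a negative result with 90% power when its power was much lower. If r = 0.3 was really intended, the study recruits far more people than its own assumption needs.

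**Working it through.** **Inputs.** From section 2.6: N = 517, power 0.9, alpha 0.05, effect 0.3 labelled r, drop-out 10%. From section 2.3: four groups. From section 2.7: chi-square and ANOVA. Two-sided testing is assumed unless noted. Evaluable number after 10% loss: 517 × 0.9 = 465.3, taken as 465.

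**Step 1: try to reproduce 517 with an effect of 0.3.**

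- *Correlation, Fisher z.* n = ((1.960 + 1.282) / atanh(0.3))² + 3 = (3.242 / 0.3095)² + 3 = 112.7, so 113. With drop-out: 125 (× 1.1) or 126 (÷ 0.9).
- *Chi-square, N = λ / w².* With four groups and c categories, df = 3(c − 1). A two-category feature gives df 3; the five tongue colours in section 2.5.1 give df 12. The noncentrality λ for 90% power is 14.17 (df 3) and 21.83 (df 12). Dividing by 0.09 gives 158 and 243. With drop-out: 174 to 270.
- *One-way ANOVA, four groups, f = 0.3 (noncentral F).* N = 164. With drop-out: 181 to 183.
- *Stretching the inputs.* The four-group ANOVA with a Bonferroni correction for 54 tests needs 300 (330 to 334 with drop-out). A chi-square would need about 68 df to reach the evaluable number implied by 517.
- *Logistic regression.* Not checkable, because no odds ratio or event rate is given.

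None of the checkable options gives 517.

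**Step 2: find what does give 517.** For a two-sided, two-sample t-test the noncentrality is d × √(n₁n₂ / (n₁ + n₂)).

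- With d = 0.3 and 235 per group: 0.3 × √117.5 = 3.25, power 0.9007. With 234 per group power is 0.8994, so 235 is the minimum and the total is 470.
- 470 × 1.1 = 517 exactly; 470 / 0.9 = 522.2, so 523.
- A one-sided test gives 382, or 421 to 425 with drop-out, which does not match.
- Near misses that are not planned tests: a difference of two correlations with q = 0.3 (474, then 522 to 527), and four times the single-correlation number (452, then 503 with ÷ 0.9).

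The two labels describe different effects. For equal groups, d = 0.3 is r = 0.3 / √(0.09 + 4) = 0.148, while r = 0.3 is d = 0.6 / √(1 − 0.09) = 0.63.

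**Step 3: power for the four-group study at 465 evaluable.**

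| Reading of the effect | Comparison | Power |
|---|---|---|
| w = 0.3 | chi-square, df 3 to 12 | > 0.99 |
| f = 0.3 | four-group ANOVA | > 0.99 |
| d = 0.3 | pairwise, 116 v 116 (noncentrality 0.3 × √58 = 2.28) | 0.62 |
| d = 0.3 | ANOVA, one of four equal groups differs (f = 0.3 × √3 / 4 = 0.130) | 0.64 |
| d = 0.3 | ANOVA, other patterns with a range of 0.3 (f = 0.106 to 0.15) | 0.46 to 0.78 |
| d = 0.3 | pairwise, 47 v 70 (10% and 15% of 465, assumed) | 0.35 |

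**Step 4: effects detectable with 90% power at 465 evaluable.**

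- Chi-square: w = √(14.17 / 465) = 0.17 (df 3) to √(21.83 / 465) = 0.22 (df 12).
- Pairwise: d = 0.43 for 116 v 116, and d = 0.62 for the assumed 47 v 70.

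**The case against.** The best reply has four parts.

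**The origin is reverse-engineered.** Section 2.6 names no test, and the full protocol behind the article may name one. This stands. A reader might take the exact match as proof that a t-test with d = 0.3 was run. The article does not show that, and the match also depends on multiplying by 1.1. The mismatch between inputs and total does not rest on this inference.

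**The study may not be underpowered.** This also stands. A reader might infer a loss of power outright, but with 0.3 on the w or f scale the omnibus power exceeds 0.99. The shortfall arises only if d = 0.3 was meant.

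**The 90% is never tied to four groups.** Section 2.6 does not say which comparison it covers, and section 2.7 does not mention pairwise tests. So the article makes no explicit false claim about a four-group contrast. But the Discussion says that differences among gastritis, ulcer disease and GERD are of interest, and a reader has no other comparison to attach the power to. A binary logistic model might offer a two-group reading, but it cannot be checked.

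**Group sizes are unknown.** The Introduction says that more than half of the world's "population suffers from gastritis to some degree", and gives low figures for ulcer incidence and East Asian GERD prevalence. A reader might infer the group split from these. They are population figures, whereas section 2.2 recruits gastroenterology outpatients and health-check attenders eligible for endoscopy. They do not fix the mix, so 47 v 70 is only an illustration.

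Condensed reporting is not an answer to the main point: the article gives both the number and its inputs, and they disagree.

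**Conclusion.** The point holds as a failure of the stated inputs to give the stated total. A correlation, the planned chi-square and the planned four-group ANOVA, each at 0.3, need 113 to 243 evaluable, or about 125 to 270 with drop-out, against 517. Logistic regression is left open.

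The 90% does not describe the four-group study on either reading. It is too low if the effect is 0.3 on the w or f scale. It is too high if d = 0.3 was meant: 0.62 for a pairwise contrast and 0.64 for the omnibus ANOVA in the pattern shown, and lower where a group is small. These figures assume 465 evaluable, two-sided 5% tests without multiplicity correction, and equal groups except where stated.

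The drop-out inflation is minor: 517 rather than 523, with power 0.898 at 465 evaluable in the two-group test.

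**What to change.** Keep 517 and restate section 2.6.

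1. Name the test, its sidedness, the number of groups and the effect metric actually used.
2. Correct the effect label. If the sponsor confirms the two-group t-test, write d = 0.3 (r of about 0.15 for equal groups) in place of r = 0.3. If the origin was different, state it with inputs that reproduce the total.
3. State what about 465 evaluable delivers for the planned four-group analyses: 90% power for w of about 0.17 (df 3) to 0.22 (df 12). If pairwise contrasts are to be interpreted, add d of about 0.43 for 116 v 116 and 0.62 for 47 v 70, marking those sizes as assumptions.
4. Say which comparison the 90% refers to.

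The cost is wording in one section. No extra patients are needed and the analysis does not change. The downside is that the stated power for group contrasts may become less favourable.
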